### 2.4. Assessments

Outcome data are gathered at four timepoints: baseline (T1), after the first eight-week intervention phase (T2), after the four-week washout (T3), and after the second intervention phase (T4) - an overview can be found in Table 1. The primary endpoint is the GIQLI, indicating changes in subjective GI health [45]. The GIQLI is a questionnaire consisting of 36 questions assessing health-related quality of life in GI disorders, each on a scale from 0 to 4 [46]. It captures a person’s own perception of symptoms, functional limitations, and the psychosocial impact thereof. The GIQLI can range from a score of 0 to 144, with higher scores indicating better gut health and satisfaction with gut health.

Secondary endpoints cover gastrointestinal transit, systemic and mucosal biology, and safety. GITT is measured in the home setting with the Blue Dye Method, defined as the interval between ingestion of blue food coloring on an empty stomach and the first and last appearance of blue-colored stool [47,48]. Blood serum collected at each visit is analyzed with the Olink Target 48 Cytokine panel (Olink Proteomics AB, Uppsala, Sweden), which quantifies 45 inflammation-related proteins, including cytokines and chemokines such as IL-2 and TNF-α. These markers have been shown to be elevated in the serum of individuals with chronic SCI patients compared to healthy controls [49]. Fecal microbial community structure is characterized by full-length 16S rRNA gene sequencing on the MinION Nanopore sequencer (Oxford Nanopore Technologies, Oxford, UK). DNA is extracted with the QIAamp PowerFecal Pro DNA kit (QIAGEN, Hilden, Germany) using ten-minute bead-beating with 0.1 mm zirconia beads, quantified with Qubit™ 4.0 dsDNA HS fluorimeter (Thermo Fisher Scientific, Waltham, MA, USA), and prepared with the MinION Nanopore Ligation Sequencing Kit (SQK-LSK114) plus native barcodes (EXP-PBC096) (Oxford Nanopore Technologies, Oxford, UK). Libraries are pooled equimolarly, loaded on R10.4.1 flow cells, and base-called with Dorado; reads below a quality score of 9 are discarded. Emu assigns taxonomy. Supplement tolerance and all adverse events are documented throughout the study.

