## 3. Data Analyses

An intention-to-treat analysis will be conducted to minimize potential bias resulting from disruption to baseline equivalence following randomization, which may occur due to participant withdrawal, non-adherence to the study protocol, or excessive missing data. Participants will be included in analyses only where data are available. Protocol deviations, early withdrawals, and loss to follow-up will be documented and evaluated. Basic univariable statistical analysis techniques will be used to describe the study population as well as the primary and secondary outcomes at the different measurement points. To evaluate the longitudinal variation in the primary outcome and secondary outcomes, we will use multilevel mixed-effects models that appropriately account for the within- and between-individual sources of variance in outcome variation. In these models, participants are treated as random effects, while intervention and period are used as fixed effects. All models will be adjusted for the baseline value of the respective outcome measured before each period. To evaluate potential carryover effects, sequence (AB vs. BA) will be included as a fixed effect, and treatment-by-period interactions will be tested. Furthermore, pre-period baselines will be compared to verify that the gut environment returned to its SCI-baseline during washout, and a carryover term will be incorporated into the model to identify residual effects. If significant carryover is detected, a sensitivity analysis using only period 1 data will be performed to provide an unbiased estimate of the intervention effect. Depending on the findings, subgroup analyses may be performed for personal parameters (e.g., sex, lesion level). For the microbiome analyses, diversity indices will be compared using paired *t*-tests while correcting for multiple testing using the Benjamini–Hochberg method. A significance level of 5% will be applied. Protein concentrations will be reported as absolute abundances in pg/mL. Absolute abundance will be tested with mixed-effects models analogous to the primary analysis. The Benjamini–Hochberg procedure will control the false-discovery rate at 5%. Multi-omics integration will employ sparse partial least-squares regression to relate inflammatory proteins, microbial genera, and clinical outcomes (GIQLI, GITT). Statistical software packages to be used include R (Version 4.5.2), Stata (Version 19.0), and SPSS (Version 31.0), or any newer stable version available at the time of data analysis.

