## 4. Strengths and Limitations

GI dysfunction is a highly prevalent and burdensome complication in SCI, often resulting in reduced quality of life and compromised autonomy. Despite its significance, effective and targeted therapeutic strategies remain limited. This study presents a unique approach by utilizing pro- and prebiotics to target the microbiome and gut dysbiosis. This study employs a crossover design, which is particularly advantageous in controlling for inter-individual variability, a known confounding factor in microbiome-related research [52,53,54,55]. The clear strength of the crossover design is that each participant acts as his own control by receiving both supplements. Further, statistical power is higher, and the required sample size to detect meaningful effects is lower compared to a parallel-group RCT [56]. An additional strength is the concurrent profiling of the fecal microbiome and 45 circulating inflammatory proteins, which supports mechanistic interpretation of clinical findings. The standardized processing pipeline and inclusion of internal controls enhance analytical reproducibility. A similar protocol implemented in wheelchair athletes, of whom the majority had a SCI, demonstrated its feasibility in this population [34].

The combination of subjective and objective outcome measures ensures meaningful findings to be detected and to hold translational relevance. The usage of commercially available supplements enhances the potential for a real-world, feasible intervention in clinical and community-based settings, outside of research, and increases the scalability of the findings. Based on previous experience in the pilot study, a sample size of 50 is realistically achievable.

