## Figures and Tables

**Figure 1 mps-09-00014-f001:**
[figure not shown]
Summary of study design. Participants are randomized into a supplement group. Supplements have to be taken daily for eight weeks (T2), followed by a four-week washout (T3) and a crossover to the other intervention for another eight weeks (T4).

**Table 1 mps-09-00014-t001:** Overview of assessments and data collection at the measurement timepoints: T1 (baseline), T2 (after first intervention), T3 (after washout), T4 (after second intervention).

	T1	T2	T3	T4
Timepoint	Week 1	Week 8	Week 12	Week 20
Location	Study center	Study center	Study center	Study center
Sociodemographic Characteristics 	X			
Changes in Diet and Medication 	X	X	X	X
GIQLI 	X	X	X	X
LTPAQ-SCI 	X	X	X	X
ISAFSCI 	X	X	X	X
Blood Sample 	X	X	X	X
Location	At home	At home	At home	At home
Stool Sample 	X	X	X	X
GITT 	X	X	X	X
3-Day Food Diary 	X	X	X	X

Note: GIQLI = Gastrointestinal Quality of Life Index, GITT = gastrointestinal transit time, ISAFCSI = International Standards to Document Remaining Autonomic Function after Spinal Cord Injury, LTPAQ-SCI = Leisure Time Physical Activity Questionnaire for persons with spinal cord injury.

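### The sparse PLS integration of proteins, genera, GIQLI and GITT is given no within-participant structure, so its components can reflect stable differences between people rather than supplement-related change

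*Protocol article*

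**What the plan says.** The article gives the integration one sentence, in section 3 (Data Analyses): "Multi-omics integration will employ sparse partial least-squares regression to relate inflammatory proteins, microbial genera, and clinical outcomes (GIQLI, GITT"). It does not say which visits form the rows, and it names no participant, intervention or period element.

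The data are repeated. Section 2.4 says: "Outcome data are gathered at four timepoints: baseline (T1), after the first eight-week intervention phase (T2), after the four-week washout (T3"), with T4 after the second intervention phase. Table 1 lists the GIQLI, blood sample, stool sample and GITT at all of "T1 (baseline), T2 (after first intervention), T3 (after washout), T4 (after second intervention").

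The other comparative analyses in section 3 do carry person structure:

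- Primary and secondary outcome models: "participants are treated as random effects, while intervention and period are used as fixed effects".
- Proteins: "Absolute abundance will be tested with mixed-effects models analogous to the primary analysis".
- Microbiome: "diversity indices will be compared using paired *t*-tests while correcting for multiple testing".

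Section 4 (Strengths and Limitations) praises the crossover design, "which is particularly advantageous in controlling for inter-individual variability, a known confounding factor in microbiome-related research". It also counts the joint profiling of microbiome and proteins as a strength, "which supports mechanistic interpretation of clinical findings".

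**The concern.** A mechanistic reading of supplement effects asks a within-person question: when a participant's supplement changes, do that participant's proteins, genera and symptoms move together? Sparse PLS in its standard form maximises covariance between blocks over all rows and treats rows as exchangeable. With several visits per person as rows, that covariance has two parts. One is between people and reflects whatever is stable about them, for example lesion level, medication or habitual diet. The other is within people and contains the response to the supplements. The method does not separate the two.

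This is the only analysis described that links proteins, genera and clinical outcomes jointly. A network built mainly on stable traits could be read as a mechanism of supplement action, and a real within-person link could be hidden behind larger differences between people. The crossover collects the data needed to avoid this, but the integration sentence does not use them that way.

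**Working it through.** The article states no figure for the integration, so there is nothing to reproduce. The checks show how large the problem can be if visits are entered as rows.

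**Inputs from the article:** 50 participants (section 2.1), four visits and 45 proteins (section 2.4), giving 50 × 4 = 200 rows.

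**Inputs assumed:** ICC, size of the supplement effect, strength of any shared person factor, and 100 genera.

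**Check 1: one protein-genus pair, no association at any level.** When both variables have the same ICC and four visits are pooled, the variance of the correlation is inflated by about 1 + 3 × ICC². A nominal 5% two-sided test then rejects when a standard normal exceeds 1.96 / √(1 + 3 × ICC²) in absolute value.

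| ICC | 1 + 3 × ICC² | 1.96 / √ | Approximate false positives | Simulated (1,000 runs) |
|---|---|---|---|---|
| 0.4 | 1.48 | 1.61 | 11% | 11% |
| 0.6 | 2.08 | 1.36 | 17% | 18% |
| 0.8 | 2.92 | 1.15 | 25% | 26% |

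The person-centred test stayed at 4% to 6%. The article plans no such pairwise test; this only shows how far 200 pooled rows overstate the information.

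**Check 2: what sparse PLS selects.** One component was fitted by soft-thresholded singular value decomposition, keeping 10 variables per block, with 40 runs per setting. In each block, 10 variables shared a stable person factor and 10 responded to the probiotic. With 10 of each kind among 100 genera, chance selection is 10 / 100 = 10% for each. The effect is the supplement's share of within-person variance. The person factor is the shared part of between-person variance.

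| ICC | Effect | Person factor | Pooled: person genera | Pooled: supplement genera | Centred: supplement genera |
|---|---|---|---|---|---|
| 0.2 | 0.3 | 0 to 0.5 | 0% | 100% | 100% |
| 0.2 | 0.1 | 0.5 | 64% | 7% | 84% |
| 0.5 | 0.3 | 0 to 0.1 | 1% | 86–89% | 100% |
| 0.5 | 0.1 | 0 to 0.1 | 10–15% | 9% | 82–85% |
| 0.5 | 0.1 to 0.3 | 0.3 to 0.5 | 66–97% | 0–15% | 84–100% |
| 0.7 | 0.1 to 0.3 | 0 to 0.1 | 10–21% | 11–12% | 83–100% |
| 0.7 | 0.1 to 0.3 | 0.3 to 0.5 | 86–99% | 0–3% | 82–100% |

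In the ICC 0.7 rows with little or no person factor, supplement genera were picked at about the chance rate even when the effect was large. In every setting simulated, the centred fit selected person-factor genera 0% to 3% of the time.

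**Check 3: tuning.** At ICC 0.6 with no association at all, 5-fold cross-validation by row gave a mean first-component correlation of 0.34, against about 0 when whole participants were held out (100 runs per setting). Row-wise folds put the same person in the training and test sets. Participant-wise folds alone are not enough: with only a shared between-person factor (loadings 0.5 and 0.7), pooled sparse PLS still gave 0.37 and 0.73, while the within-person fit gave about 0.

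**The case against.** The strongest reply is that the defect is read from silence. The sentence does not say that visits are pooled, and change scores or a multilevel version are not excluded. A condensed article may leave component counts, sparsity and fold structure to a fuller plan. Its authors clearly recognise the repeated structure, since their other models handle it. All of that is fair, and a reader who infers that a pooled fit with row-wise tuning is planned goes beyond the text. What remains is that the choice between a between-person and a within-person analysis decides which question is answered. Section 3 states that choice for its other comparative analyses and not for this one.

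Other parts of the reply also stand:

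- The statement about mechanism in section 4 concerns concurrent profiling, not sparse PLS by name, and supplement effects on proteins have their own mixed models.
- Relating the blocks across people is a legitimate descriptive aim, provided that it is labelled so.
- A single visit is not free of supplement information: at T2 the supplement is randomised between people. But a T2-only fit leaves stable differences in place and forgoes the crossover comparison.
- Every ICC and effect size above is assumed, and the result reverses when the ICC is low and the effect large.
- Centring does not remove period effects and does not by itself prove mechanism.

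**Conclusion.** The point holds in a conditional form. The named method has no within-participant structure. If visits are entered as rows in its standard form, the components mix two kinds of covariance and can be dominated by stable differences between people. Under the assumed settings this happened at ICC 0.5 to 0.7 with a moderate shared person factor. It also occurred at ICC 0.2 when the effect was small and the person factor strong. It did not occur at ICC 0.2 with the larger effect, or at ICC 0.5 with the larger effect and little shared factor. The article gives no ICC, so it cannot be known which case applies.

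Two stronger readings are tempting and are not supported. One is that the integration will mainly pick up stable differences between people; that depends on quantities the article does not give. The other is that it cannot support any mechanistic interpretation. The supported statement is that a pooled result would not, by itself, justify a mechanistic reading of supplement effects. The primary GIQLI analysis and the protein mixed models are untouched. This is a worthwhile correction to a secondary analysis.

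**What to change.** In section 3, replace the integration sentence with wording to this effect: multi-omics integration will use multilevel (within-participant) sparse PLS, fitted to values centred on each participant's own mean; the pre-to-post changes (T2 − T1 and T4 − T3) will be analysed the same way as a sensitivity analysis; the number of components and the sparsity will be tuned by leave-participant-out cross-validation.

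Report any sparse PLS on between-person differences separately and label it as association. In section 4, rest any mechanistic statement about supplement effects on the within-participant result.

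The cost is a few lines of text and a centring step before the same kind of fit, with no new data or participants. The downside is that purely between-person associations leave the main integration result.

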
### Patient and Public Involvement Statement

There was no involvement of patients or the public in the design, conduct, reporting, or dissemination planning of this trial. However, the research addresses priorities identified by individuals with SCI, particularly bowel management and discomfort in daily life [4,6]. Findings will be shared with the community in appropriate formats, online, and in magazines.

## 4. Strengths and Limitations

GI dysfunction is a highly prevalent and burdensome complication in SCI, often resulting in reduced quality of life and compromised autonomy. Despite its significance, effective and targeted therapeutic strategies remain limited. This study presents a unique approach by utilizing pro- and prebiotics to target the microbiome and gut dysbiosis. This study employs a crossover design, which is particularly advantageous in controlling for inter-individual variability, a known confounding factor in microbiome-related research [52,53,54,55]. The clear strength of the crossover design is that each participant acts as his own control by receiving both supplements. Further, statistical power is higher, and the required sample size to detect meaningful effects is lower compared to a parallel-group RCT [56]. An additional strength is the concurrent profiling of the fecal microbiome and 45 circulating inflammatory proteins, which supports mechanistic interpretation of clinical findings. The standardized processing pipeline and inclusion of internal controls enhance analytical reproducibility. A similar protocol implemented in wheelchair athletes, of whom the majority had a SCI, demonstrated its feasibility in this population [34].

The combination of subjective and objective outcome measures ensures meaningful findings to be detected and to hold translational relevance. The usage of commercially available supplements enhances the potential for a real-world, feasible intervention in clinical and community-based settings, outside of research, and increases the scalability of the findings. Based on previous experience in the pilot study, a sample size of 50 is realistically achievable.

The study is subject to several limitations. The open-label nature of the study might introduce a potential bias. With the probiotic packaging resembling a medicinal product, versus the prebiotic clearly coming from a grocery store, participants may have different expectations for the efficacy of either supplement, which may bias their responses. This is not preventable, given the need for specific packaging for both supplements. Additionally, as diet and lifestyle are not strictly controlled, microbiome changes may be confounded, which in a real-life setting cannot be avoided. Despite not being controlled, by assessing physical activity and nutrition at each timepoint, big lifestyle changes can be detected and taken into consideration when analyzing the data. Further, at home supplementation makes strict control of adherence impossible; however, by asking participants to return empty packages after the intervention period, a sense of control is added and quantification of adherence is possible.

Another potential limitation of this crossover design is the risk of carryover effects, where the physiological and microbial changes from the first intervention might persist into the second period. Given the neurogenic bowel dysfunction inherent in SCI, transit times are prolonged, which could theoretically extend the influence of interventions. However, this risk is mitigated by the implementation of a 4-week washout period, exceeding the 2-week window typically required for the microbiome to revert to baseline after a dietary perturbation, and by employing a rigorous four-tiered statistical framework to detect sequence and period interactions [57,58,59,60].

## 5. Conclusions and Outlook

With GI discomfort and bowel management being priorities of the community with SCI, and the high numbers of affected people within the community, studies like this are very much needed. Both probiotic and prebiotic supplementation will be evaluated as potential treatment avenues for GI discomfort and gut dysbiosis. The effects will be measured by both patient-reported outcomes, e.g., GIQLI, and objective measures, e.g., microbiome composition, blood inflammation markers, and GITT, and we aim to assess changes in gut health and gut health-related quality of life. The inclusion of subjective and objective measures enhances translational relevance.

Compared to existing research, this study advances the field by addressing an underexplored intersection between microbiome science, GI health, and quality of life in SCI. Findings from this study will be shared with the clinic and the community with SCI to allow for more informed consulting of patients with SCI and GI dysfunction. This may lower the burden of bowel problems in SCI in the long-term and improve experienced quality of life for affected persons.

## Figures and Tables

**Figure 1 mps-09-00014-f001:**
[figure not shown]
Summary of study design. Participants are randomized into a supplement group. Supplements have to be taken daily for eight weeks (T2), followed by a four-week washout (T3) and a crossover to the other intervention for another eight weeks (T4).

**Table 1 mps-09-00014-t001:** Overview of assessments and data collection at the measurement timepoints: T1 (baseline), T2 (after first intervention), T3 (after washout), T4 (after second intervention).

	T1	T2	T3	T4
Timepoint	Week 1	Week 8	Week 12	Week 20
Location	Study center	Study center	Study center	Study center
Sociodemographic Characteristics 	X			
Changes in Diet and Medication 	X	X	X	X
GIQLI 	X	X	X	X
LTPAQ-SCI 	X	X	X	X
ISAFSCI 	X	X	X	X
Blood Sample 	X	X	X	X
Location	At home	At home	At home	At home
Stool Sample 	X	X	X	X
GITT 	X	X	X	X
3-Day Food Diary 	X	X	X	X

Note: GIQLI = Gastrointestinal Quality of Life Index, GITT = gastrointestinal transit time, ISAFCSI = International Standards to Document Remaining Autonomic Function after Spinal Cord Injury, LTPAQ-SCI = Leisure Time Physical Activity Questionnaire for persons with spinal cord injury.

## Data Availability

In this study protocol, no data was collected or analyzed. Data sharing thus does not apply to this article.

## Abbreviations

The following abbreviations are used in this manuscript:

AIS	American Spinal Injury Association Impairment Scale
CFU	Colony Forming Units
GIQLI	Gastrointestinal Quality of Life Index
GI	Gastrointestinal
GITT	Gastrointestinal Transit Time
ISAFSCI	International Standards to Document Remaining Autonomic Function After Spinal Cord Injury
LTPAQ	Leisure Time Physical Activity Questionnaire
RCCT	Randomized Controlled Crossover Trial
SCI	Spinal Cord Injury

## Appendix A

**Table A1 mps-09-00014-t0A1:** Overview of sociodemographic data collected at each timepoint. AIS Score = American Spinal Injury Association Impairment Scale, SCI = spinal cord injury, GI = gastrointestinal.

Variable	Specification	Timepoint
Year of Birth		Screening
Sex	Female: currently pregnant?	Screening
Date of SCI		Screening
AIS Score		Screening
Antibiotics	Yes/no during the past 4 weeks	Screening
Height		T1
Body Mass		T1, T2, T3, T4
Cause of SCI	Traumatic or non-traumatic	T1
Lesion Level		T1
GI Disease		Screening, T1
Further Diseases		T1
Medication Intake		Screening, T1, T2, T3, T4
Diet	Normal, vegetarian, vegan, etc.	Screening, T1, T2, T3, T4
Sports	Sport type and hours training per week	T1
